#### Outcomes: Social Capital

The outcome variable of interest for the RCT—social capital—includes cognitive and structural dimensions [14]. The cognitive dimension of social capital is operationalized to include youth feelings of belonging, support in relationships, and trust. Feelings of belonging will be measured using a question from the European Social Survey (ESS) Round 8 [42] on how connected the youth feel to Norway. The response scale ranges from 0 (“not emotionally connected at all”) to 10 (“very emotionally connected”).

Youth will also be asked about how often they felt lonely during the previous month (five-point scale: “not at all” to “all the time”) (similar to a question from a Statistics Norway survey on social relations [43] and questions in the ESS [42]).

Shared language is another indicator of cognitive social capital related to belonging [44]. This will be measured by using a self-created question asking: How comfortable are you speaking Norwegian? (scale from 1=“very uncomfortable” to 5=“very comfortable”).

Trust will be measured using the question on generalized trust (A4) from the ESS [42] with a response range from 0 to 10 (“you can’t be too careful” to “most people can be trusted”).

The structural dimension of social capital relates to the presence and patterns of connections between actors or network characteristics (bridging, bonding, linking), school connectedness, and civic engagement or organizational participation. To assess network characteristics, the respondents will be asked about the proportion of their friends with a similar ethnic background and religion (bonding), with an immigrant background (bonding), and with a Norwegian background (bridging). This will be assessed using a five-point scale (“none” to “all”; similar to [22,45]).

Civic engagement will be measured using questions about organizations in which the youth are active. The youth will be provided with a list of different organization types (religious, sports, art and music, volunteer organization) and will be asked to respond if they are a member, have participated previously, or are not a member (similar measures are used in ESS and in the Ungdata survey for Norwegian adolescents [46]).

Patterns and nature of contact with friends and family will be measured in several ways. The youth will be asked if they have at least one good friend that they can fully trust (four-point scale from “no, I have no one I would call a friend at the moment” to “yes, for sure”) (questions are taken from Ungdata [46]). Respondents will also be asked about frequency of contact with their friends outside of school or work [42], with responses on a six-point scale from “never” to “every day” (similar to [45]).

To measure school social capital and connectedness, several dimensions (teachers, classmates, school) will be used. Connectedness will be measured using indicators from the Health Behavior in School-aged Children study protocol questionnaire [47], as used in a Swedish study on social capital [4]. Connectedness with teachers will be measured with three items (five-point scale from “strongly disagree” to “strongly agree”); for example, “I feel that my teachers accept me as I am.” Connectedness with classmates will be measured using three items (eg, “most of the students in my classes are kind and helpful”) with the same five-point scale. These two scales have been validated using confirmatory factor analysis [47]. To assess connectedness with school, three questions from Ungdata [46] (“I am often bored at school,” “I don’t like going to school,” and “It’s important to do well at school”) will be used, also with a five-point scale. One question from the Health Behavior in School-aged Children [47] (“How do you feel about school at present”) will also be used (4-point response scale from “I like it a lot” to “I don’t like it at all”). To assess school attachment, a self-developed item similar to that used in Ungdata [46] will be used to assess if and how often the youth have considered dropping out of school in the previous three months. Response alternatives (four-point scale) range from “never” to “very often.”

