The full-scale RCT will recruit participants from Norwegian schools and include both a control and an intervention group. The study will try to select similar schools for both groups regarding school size, socioeconomic characteristics, and school type (age range of the student body). Within the intervention group of schools, intervention classes will be drawn randomly, whereas control classes will be drawn randomly from the control schools. Participants and nonparticipants will not attend the same schools to avoid contagion effects. The exact number of individuals will be estimated based on a power analysis of data from the pilot study and is anticipated to encompass several hundred youth. Half will be in the intervention group and half in the control group. Students who are not assigned to the control groups for the study will have the opportunity to receive the intervention after the study has concluded. Although all the youth will have a basic level of Norwegian proficiency, additional potential inclusion and exclusion criteria for the RCT will be developed based on findings from the pilot study. Similar to the pilot study, mentors will be surveyed at program conclusion, and respondents will be invited to qualitative interviews and focus groups, to supplement and nuance the quantitative data.

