### Data Collection Procedure

#### Pilot Study

After receiving information about the project in the form of a video and giving informed consent, the mentees will receive an individual link to participate in a Web survey. Questions on the mentee survey at program commencement will focus on social capital in the form of relationships with friends, native Norwegians, connectedness to the school environment, and to Norway more broadly. This will be used to test out and adjust measures for the full RCT study based on feedback from the groups. A Web survey will be administered at program completion, with the same survey questions as on the first survey, supplemented with questions about program fidelity (outputs) and a short battery to assess the relationship with the mentor and implementation. Mentors will receive surveys related to program fidelity and the relationship with mentees and staff. Additionally, both mentees and mentors will respond to survey questions on the usability of the digital platform. To supplement the quantitative survey data, qualitative data will be collected from mentors and mentees in interview form for both the pilot and RCT. Individuals will be selected for interviews based on characteristics such as age, sex, immigration background, and length of time in Norway, with a goal to get a very diverse group [38]. Interview questions will address barriers and facilitators to implementation, possible contextual factors relevant to the implementation and participants’ experiences of these factors, and the acceptability and meaningfulness of the measures used in the survey (see Outputs in the Measures section for details on the operationalization of these concepts). Questions to program staff will focus on resources such as program staffing, finances, and technical support for the digital platform.

The pilot study has been approved by the Data Protection Office at Oslo University Hospital. All pilot study data will be stored on a secure remote server as per Oslo University Hospital Personal Data Protection regulations. The pilot study is funded by a grant from the Norwegian Research Council and is a partnership between the Center for Shared Decision Making and Collaborative Care Research at Oslo University Hospital, NORCE-Norwegian Research Centre, Halmstad University, the Norwegian Labor and Welfare Administration (NAV), and Fretex.

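### The civic engagement item asks where youth are active but its answers mix membership with participation, leave no place for current participation without membership, and overlap

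*Protocol article*

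**What the plan says.** In the protocol article, under Outcomes: Social Capital, the structural dimension includes "school connectedness, and civic engagement or organizational participation". The measure is introduced with "Civic engagement will be measured using questions about organizations in which the youth are active". Youth are given a list of organization types (religious, sports, art and music, volunteer) and "will be asked to respond if they are a member, have participated previously, or are not a member". On the origin of the item, the article says that "similar measures are used in ESS and in the Ungdata survey for Norwegian adolescents"; the wording of those source items is not shown.

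On the item's standing, "The outcome variable of interest for the RCT—social capital—includes cognitive and structural dimensions", and civic engagement is one of many indicators listed for those dimensions. No scoring rule for the three answers is given. The Pilot Study section says of the baseline survey: "This will be used to test out and adjust measures for the full RCT study based on feedback from the groups".

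**The concern.** The construct and the stem concern being active now. The answers concern being a member now or having taken part in the past. The first mixes two attributes that need not go together, and the combination of taking part now without being a member is missing. That combination is plausible here. One listed type is volunteer organizations, where taking part need not imply membership. A mentor who helps a recently arrived youth into a new activity over six months may well produce informal attendance before formal membership.

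What is at stake is whether an arm difference on this indicator can be read as a difference in participation. A scoring rule written later can deal with overlapping answers, but it cannot recover a category that was never collected.

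**Working it through.** **Step 1. Set the possible states against the answers, read literally.**

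| True state of the youth for one organization type | Answers that fit |
|---|---|
| Takes part now, is a member | member |
| Takes part now, is not a member | not a member; or participated previously, if earlier sessions are counted |
| Member, does not take part | member |
| Took part before, not now, not a member | participated previously **and** not a member |
| Never took part | not a member |

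Three defects follow from the text alone:
- The second state has no answer of its own. It shares a code with never having taken part or with having quit.
- Active and inactive members share a code.
- The past and non-member answers overlap, so the same youth can move between them from one survey to the next with no real change.

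**Step 2. What the article lets one compute.** It gives no participation rate, effect size, non-member share or scoring rule for this item. The sample size is still open: "The exact number of individuals will be estimated based on a power analysis of data from the pilot study". Allocation is equal: "Half will be in the intervention group and half in the control group". There is therefore no figure to reproduce, and what follows only illustrates direction and order of size.

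Assumptions, none of them from the article:
- True current participation is p_C = 0.30 in control and p_I = 0.40 in intervention.
- Only the answer 'member' is scored as participating.
- A share q of current participants are non-members, and a fraction m of these tick 'member' anyway.
- There are no inactive members.
- Tests are two-sided at 5%, at individual level, with clustering ignored.

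Observed proportion in an arm = p × [1 − q(1 − m)].

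**Step 3. Same q in both arms, m = 0.** The observed difference is 0.10 × (1 − q). The second-last column holds the sample at the 356 per arm that gives 80% power when q = 0.

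| q | Control | Intervention | Difference | Ratio | Power at 356 per arm | Per arm for 80% power |
|---|---|---|---|---|---|---|
| 0 | 0.300 | 0.400 | 10.0 points | 1.33 | 80.0% | 356 |
| 0.10 | 0.270 | 0.360 | 9.0 points | 1.33 | 73.5% | 417 |
| 0.25 | 0.225 | 0.300 | 7.5 points | 1.33 | 62.4% | 540 |
| 0.50 | 0.150 | 0.200 | 5.0 points | 1.33 | 41.9% | 906 |

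The difference shrinks and the ratio does not. Because the trial is cluster randomized, the power and sample size columns do not describe this design; they show only the pattern.

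**Step 4. Non-member share confined to the newly gained participation.** If a share s of the 10-point gain is non-member participation scored as none, the observed gain is 10 × (1 − s). This is 5 points at s = 0.5 and 0 at s = 1.

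**Step 5. Non-members who tick 'member'.** With q = 0.5 in both arms, the observed difference is 0.10 × [1 − 0.5(1 − m)]: 5.0 points at m = 0, 7.5 at m = 0.5 and 10.0 at m = 1. The loss can be partial or nil.

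**Step 6. The opposite direction.** Let participation be 40% in both arms, with non-member shares of 50% in control and 25% in intervention, because mentoring moved some existing participants into membership. With m = 0, the observed difference is 0.40 × 0.75 − 0.40 × 0.50 = 0.30 − 0.20 = 0.10. The item shows a 10-point effect where participation does not differ.

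**The case against.** The strongest objection is that the article may be summarizing the questionnaire. Most other response labels in the measures sections stand in quotation marks and these do not, so 'member' may be shorthand for current involvement. That is possible. However, the article states three answers and shows nothing else, and similarity to other surveys whose wording is not shown does not make these answers fit this stem. If the actual form already has the category, the remedy is to correct the description.

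Second, the item is provisional. The pilot asks whether the measures are valid and meaningful to stakeholders, and Table 1 schedules interviews on the relevance of the social capital measures. This stands, and it makes the correction timely. It does not supply the missing answer, and the article does not name this problem as something to look for.

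Third, the item carries limited weight. It is one of many indicators, and the working hypothesis in the Discussion names networks, trust and belonging rather than organizational participation. This stands and limits the consequence.

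Fourth, a reader might infer that the item must understate the program's effect. The document does not support that. It gives no scoring rule and does not say how a drop-in participant would answer, and steps 5 and 6 show cases with no loss and with overstatement. Attenuation is the more likely direction, not an established one.

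**Conclusion.** The defect in the stated answers is real: they mix membership with participation, have no place for current non-member participation, and are not mutually exclusive. Youth in that position may be misclassified. Attenuation of an effect on participation is probable if the program raises non-member participation and those youth do not tick 'member'. Overstatement is possible if the program mainly turns existing non-member participants into members.

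The size cannot be determined from the article. The range of 9 to 5 points for a true 10-point difference rests on assumed rates, an assumed and equal non-member share in both arms, and an assumed scoring rule. It is an illustration, not an estimate for this trial. The practical consequence is that a difference on this indicator, in either direction, would be hard to read as a change in participation. This is a cheap improvement to make before the RCT, not a threat to the trial's overall conclusion.

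**What to change.** Before the RCT, revise the response set under Outcomes: Social Capital so that current participation and membership are separated and the answers exclude one another. Either of two forms would do:

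- One question per organization type. At minimum, add 'take part now but am not a member' and word the past and never answers so that only one can apply. A further answer, 'member but do not take part', would also separate inactive from active members.
- Two short questions per type: one on current participation, one on membership.

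State that organizational participation is scored from current participation, with membership reported separately if wanted. Try the revised item in a pilot survey or interview. Because the pilot completion survey repeats the baseline questions, adding the new item beside the old one there would keep the pilot's own pre-post comparison intact.

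The cost is one or two extra options per organization type and slightly less direct comparability with the source surveys.

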#### Context and Controls

Demographic characteristics of the youth in the sample, such as age, sex, length of time living in Norway, and economic status (inquiring about their finances during the past year), will also be included in the survey. Characteristics related to setting (school size and centrality) and the digital context in which the respondents participate will also be taken into account. In the pilot study, the usability of the digital platform will be assessed in a survey, which will include questions from the System Usability Scale [48], a robust tool for analyzing usability [49]. The scale has 10 items (eg, “I thought the platform was easy to use”) and response choices on a five-point scale from “strongly disagree” to “strongly agree.” Assessment of contextual factors will also be collected from mentors and youth in interview form.

### Data Analysis

Quantitative data will be analyzed using statistical software packages. Descriptive statistics will be presented and pre-post measures used to determine the impact of the intervention on social capital and more distal outcomes. Additionally, because the literature suggests that mentoring produces better outcomes for some groups (eg, high-risk male youth) over others [50], we will conduct exploratory analyses to investigate differing effects of the intervention based on age, gender, and time in Norway. All interviews will be recorded and transcribed, and qualitative analysis software (NVIVO 12) will be used on the transcribed interviews and forum data. This will entail coding of responses, first extracting broad themes from the data, and then identifying subthemes [51]. This type of qualitative analysis will supplement the data from the surveys, allowing a better understanding of the implementation process and explain why specific outcomes might have occurred [38].

## Results

This protocol was informed by a prepilot study conducted from January to June 2019 [31], which focused on the experiences and needs of stakeholders with relation to the digital mentoring platform and perceptions around the concept of social capital. This enabled the identification of areas of focus and strategy for this protocol, particularly in relation to social capital and key components of the mentoring program. Therefore, the resulting protocol is considered well-suited for providing a valid analysis of program fidelity (which the mentoring program is currently working to adhere to) and new knowledge about social capital as a health promotion intervention among immigrant youth.

The pilot study will commence in fall 2019 and conclude in spring 2020. The participants (mentors and youth mentees; approximately 40 of each) have already been identified for the pilot portion of the protocol. Efforts related to recruitment for the RCT will begin after the pilot study is finished.

## Discussion

The overall objective of this protocol was to present a plan for evaluating the implementation and effects of digitally augmented mentoring relative to social capital among immigrant youth. The main working hypothesis is that students who receive the intervention will have broader networks and higher levels of trust and feelings of belonging (greater social capital) compared with those students who do not receive the intervention. Considering the paucity of research on social capital interventions, the protocol should be relevant for researchers interested in community-based health promotion and in social capital more broadly. More specifically, it provides a framework for analyzing mentoring programs for immigrant youth to see what works under what circumstances and for whom. However, there are some anticipated limitations.

Because mentees self-select to the program in the pilot study, these findings may not be generalizable to a larger group; however, this is not the primary objective of the pilot. The RCT should ameliorate this issue owing to the random selection of individuals and classes. Another potential limitation relates to language issues, particularly in the survey instrument. The pilot study is intended to assess the relevance and acceptability of the instruments to the target groups; comprehension will also be a relevant consideration at this stage. Thus, this issue will hopefully be minimal in the RCT. Attrition, particularly after program completion, is another potential limitation, as in most survey research.

If this intervention is successful, it may have an impact on the possibility for young people to be better included in Norwegian society. Further work could potentially encompass cost-benefit analyses if there is support for the hypotheses. These preliminary results from the pilot and RCT, if positive, could be promising for a potential expansion of the intervention to other contexts and target groups.

## Appendix

Multimedia Appendix 1 Platform screenshot: Log-in screen with code access.

Multimedia Appendix 2 Platform screenshot: Overview of program activities including program "launch" and "achievement story".

Multimedia Appendix 3 Platform screenshot: Overview of program activities including "roadmap", "network mapping", and "reflection exercise".

Multimedia Appendix 4 Platform screenshot: Information on "network building".

Multimedia Appendix 5 Peer reviewer report from the Norwegian Research Council.

## Abbreviations

ESS: European Social Survey
RCT: randomized controlled trial
